## Abstract

**Background:**

Because of high demand on hospital beds, hospitals seek to reduce patients’ length of stay (LOS) while preserving the quality of care. In addition to usual intermittent vital sign monitoring, continuous monitoring might help to assess the patient’s risk of deterioration, in order to improve the discharge process and reduce LOS. The primary aim of this monocenter randomized controlled trial is to assess the effect of continuous monitoring in an acute admission ward (AAW) on the percentage of patients who are discharged safely.

**Methods:**

A total of 800 patients admitted to the AAW, for whom it is equivocal whether they can be discharged directly after their AAW stay, will be randomized to either receive usual care without (control group) or with additional continuous monitoring of heart rate, respiratory rate, posture, and activity, using a wearable sensor (sensor group). Continuous monitoring data are provided to healthcare professionals and used in the discharge decision. The wearable sensor keeps collecting data for 14 days. After 14 days, all patients fill in a questionnaire to assess healthcare use after discharge and, if applicable, their experience with the wearable sensor. The primary outcome is the difference in the percentage of patients who are safely discharged home directly from the AAW between the control and sensor group. Secondary outcomes include hospital LOS, AAW LOS, intensive care unit (ICU) admissions, Rapid Response Team calls, and unplanned readmissions within 30 days. Furthermore, facilitators and barriers for implementing continuous monitoring in the AAW and at home will be investigated.

**Discussion:**

Clinical effects of continuous monitoring have already been investigated in specific patient populations for multiple purposes, e.g., in reducing the number of ICU admissions. However, to our knowledge, this is the first Randomized Controlled Trial to investigate effects of continuous monitoring in a broad patient population in the AAW.

**Trial registration:**

https://clinicaltrials.gov/ct2/show/NCT05181111. Registered on 6 January 2022. Start of recruitment: 7 December 2021.

**Supplementary Information:**

The online version contains supplementary material available at 10.1186/s13063-023-07416-8.

## Introduction

As the demand on hospital beds increases over the years [1] and the shortage of nurses continues [2], hospitals aim to increase efficacy. Therefore, patients are discharged as early as possible when it is medically safe [3]. In the Netherlands, patients presented in an Emergency Department (ED) are commonly admitted, either for specific treatment or for further observation, to an acute admission ward (AAW). This non-intensive ward, commonly referred to as an Acute Medical Unit, has been widely implemented in multiple countries [4]. It is a ward where patients from different specialties in need of acute care are admitted to for typically 24 to 72 h prior to discharge or transfer to an in-hospital ward. During this intentionally short stay in the AAW, a patient’s risk of deterioration is assessed by intermittent vital sign monitoring and the calculation of a corresponding Early Warning Score (EWS). The frequency of this assessment is determined by the patient’s condition and typically performed every 4 to 8 h. Although for some patients the risk of deterioration is clearly low or high, for other patients it is uncertain whether deterioration will occur. Subsequently, patients with this uncertainty are often admitted to an in-hospital ward. However, the need for such an admission to an in-hospital ward is equivocal. For patients that do require in-hospital care, early detection of stability may decrease the uncertainty regarding hospitalization and provide care planners with the opportunity to allocate a bed in a suitable ward in a timely manner. Consequently, these patients are expected to be admitted to the appropriate ward sooner, potentially reducing their length of stay (LOS) in the AAW. For patients who can be discharged, the time spent in the AAW may also be reduced due to earlier confirmation of stability. The reductions of LOS and unnecessary admissions to in-hospital wards might increase the efficacy of the use of hospital beds.

The EWS consists of several parameters that may predict deterioration, of which heart rate (HR) and respiratory rate (RR) are especially predictive [5–7]. Continuous monitoring of these vital signs, which can be facilitated by wearable sensors, may therefore help to timely assess safe discharge [8]. Such sensors measure vital signs wirelessly and continuously, without reducing patient’s mobility and with potentially decreasing nurses’ workload [9–12]. Although several wearable sensors have been validated and are increasingly used in surgery wards, the use of these devices to optimize the discharge process in the AAW has not been investigated before [13, 14]. Hence, proof of clinical benefit and cost-effectiveness is still lacking [15, 16].

Therefore, the primary aim of this randomized controlled trial is to assess the effect of continuous monitoring of HR and RR on the percentage of patients who can be safely discharged directly from the AAW. Safe discharge is defined by the absence of unplanned readmissions, ED revisits, or mortality occurrences within 30 days.

## Methods

### Study setting

This trial (NCT05181111—ClinicalTrials.gov) is a monocenter randomized controlled trial with two groups and is conducted in Rijnstate Hospital, Arnhem, the Netherlands. Rijnstate is a 766-bed community teaching hospital covering an area of 450,000 inhabitants. This hospital, like most Dutch hospitals, has an AAW where patients are temporarily monitored using intermittent vital sign monitoring to assess the risk of deterioration and enhance patient flow from the ED [17]. In accordance with the local hospital protocol, all patients in need of hospitalization from the ED could be admitted to the AAW, except when patients meet certain exclusion criteria (see Table 1). Consequently, the AAW accommodates a diverse patient population, including both surgical and non-surgical patients. In 2019, there were 9077 admissions to the AAW in Rijnstate. In this trial, participating patients will be randomized to a control group receiving only usual care or to a sensor group receiving usual care with an additional wearable sensor for continuous monitoring, which is described in more detail in the intervention section. This trial protocol uses the Standard Protocol Items: Recommendations for Interventional Trials (SPIRIT) reporting guidelines (see Additional file 1) [18].

**Table 1 Tab1:** Exclusion criteria for admission to the acute admission ward of Rijnstate Hospital

Exclusion criteria for admission to the acute admission ward.	
**General**	- In need of admittance to the cardiac care unit, medium care, or intensive care - Requiring specific psychiatric care - 18 years old - Multiple fractures - In need of isolation (tuberculosis, MRSA, varicella zoster) - Requiring post-examination recovery
**Internal Medicine**	- Lymphatic leukemia - HIV that requires treatment - In need of dialysis - Renal transplant - Autologous stem cell transplantation within the last 6 months
**Pulmonology**	- In need of non-invasive ventilation - In need of >5 l/min of supplemental oxygen - Unstable after 2 h of oxygen supply via non-rebreathing mask
**Neurology**	- Only patients with minor head trauma are accepted
**Gastroenterology**	- Pancreatitis - Gastrointestinal bleeding - Choledocholithiasis and cholangitis - Inflammatory bowel disease - Gastroenterological malignancy - Liver cirrhosis
**Urology**	- Severe hematuria - Terminal disease
**Otorhinolaryngology**	- Cuffed tracheal cannula - In need of advanced airway care - Severe facial fractures
**Geriatrics**	- Severe delirium - Terminal disease

### Study population

All ED patients who are scheduled to be admitted to the AAW are screened by emergency physicians to identify those eligible for participation in this trial. This trial aims to recruit patients whose discharge destination following the AAW is uncertain upon admission, in order to effectively evaluate the impact of continuous monitoring on the discharge process. The emergency physician identifies these patients by answering the following questions: Is it certain that the patient will be discharged within the next 24 h? Is it certain that, after admission to the AAW, the patient must be transferred to an in-hospital ward? When both questions are answered “no,” the patient is considered an “equivocal patient” and is eligible for participation. Other inclusion criteria are that patients should be 18 years or older and are able to speak and read Dutch. Exclusion criteria are known pregnancy, breastfeeding, not able or willing to wear a wearable sensor for 14 days, scheduled surgery within the next 30 days, an active implantable device, any skin condition where the wearable sensor needs to be placed, known sensitivity to medical adhesives, use of creams or lotions that influence the skin at the area where the wearable sensor is placed or intend to go the sauna or swimming in the next 14 days. Patients with a pacemaker or known pregnancy are excluded from participation due to the potential influence of the pacemaker or child on the sensor measurements, respectively. Breastfeeding may be hindered by the sensor, which was deemed undesirable. Patients scheduled for surgery within 30 days are excluded as it may directly impact the primary outcome measure due to prolonged or new hospitalizations after surgery. Following the instruction for use, the manufacturer advises against swimming or visiting the sauna, as this may lead to the detachment of the sensor.

### Outcomes

The primary outcome is the difference between the control and sensor group in the percentage of patients who are safely discharged from the hospital directly after AAW stay. A safe discharge is defined as a discharge without following unplanned hospital readmission, ED revisit, or mortality within 30 days. Secondary outcomes are LOS in the AAW, LOS in the in-hospital wards, percentage of RRT calls during AAW and hospital stay, percentage of ICU admissions during AAW and hospital stay, and percentage of unplanned readmissions to the hospital within 30 days after hospital discharge. Furthermore, facilitators and barriers for implementing continuous monitoring in usual care in the AAW will be assessed by questionnaires and interviews with healthcare professionals. Also, for the sensor group, the feasibility of remote home monitoring with the wearable sensor is assessed, including the duration for which the sensor was worn, factors leading to its early detachment, user complaints regarding wearing the sensor, and restrictions in daily activities.

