### Statistics

For the descriptive analyses (e.g., characteristics of participants), continuous variables will be reported as mean with standard deviation for normally distributed data, and median with interquartile range for non-normally distributed data. For categorical variables, numbers and percentages will be reported.

For the primary outcome, the proportion of patients discharged home safely, directly after AAW stay, will be compared between the control and sensor group using a chi-squared test. Differences in LOS will be tested using Student’s *t*-test or Mann-Whitney test depending on the presence of a normal distribution. To assess whether the percentages of ICU admissions, RRT calls, and hospital admissions differ between the control and sensor groups, chi-squared or Fisher’s exact tests will be used, as appropriate. Intention-to-treat analyses will be used for the primary and secondary outcomes. Additionally, per-protocol analyses will be used to assess the effect of the sensor, adjusted for patients who receive a non-functional sensor due to technical reasons. All remaining patients will be included in these per-protocol analyses, regardless of their destination after AAW admission and the duration for which the wearable sensor was worn. An interim analysis for futility is planned once 50% of total amount of patients is included.

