**Fig. 2 Fig2:**
[figure not shown]
Upper graph: Sensor Early Warning Score based on heart rate (HR) and respiratory rate (RR). Center and lower graphs: HR (green) and RR (orange) of a patient, respectively

After admission to the AAW, patients are either discharged home, to a nursing home, or admitted to an in-hospital ward. In all cases, for patients in the sensor group, the wearable sensor remains attached for a total of 14 days. However, after AAW stay, these measurements are no longer presented to healthcare professionals, but only analyzed retrospectively. After 14 days, the wearable sensor is removed by the patient and patients of both the control and sensor group are asked to fill in the patient questionnaire. Patient follow-up will be completed 30 days after hospital discharge.

A schedule of enrolment, interventions, and assessments of this trial is shown in SPIRIT format in Table 2 [18]. Hospital readmissions, ED revisits, and mortality are monitored until 30 days after hospital discharge. At the end of the trial, healthcare professionals are asked to fill in a questionnaire to assess satisfaction and the usability of the wearable sensor. Facilitators and barriers for implementing continuous monitoring in usual care in the AAW and at home will be assessed by patient questionnaires, healthcare professional questionnaires, and interviews with healthcare professionals.

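### The Abstract and the Outcomes section name different length-of-stay outcomes, and in-hospital ward stay has no stated value for patients who are never transferred

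*Protocol article*

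**What the plan says.** All references are to the protocol article.

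- **Abstract, Methods:** "Secondary outcomes include hospital LOS, AAW LOS, intensive care unit (ICU) admissions". Hospital LOS is defined for every randomised patient.
- **Methods, Outcomes:** "Secondary outcomes are LOS in the AAW, LOS in the in-hospital wards". The list goes on to rapid response calls, ICU admissions and readmissions. Total hospital LOS does not appear.
- **Methods, Statistics:** "Differences in LOS will be tested using Student’s *t*-test or Mann-Whitney test depending on the presence of a normal distribution". No population is named for the LOS comparisons, and no value is given for a patient without a ward stay. The same section says "Intention-to-treat analyses will be used for the primary and secondary outcomes".
- **Intervention (text after Fig. 2):** after the AAW, "patients are either discharged home, to a nursing home, or admitted to an in-hospital ward". Only the last of these routes produces a ward stay.
- **Introduction:** fewer ward admissions are an intended effect: "The reductions of LOS and unnecessary admissions to in-hospital wards might increase the efficacy of the use of hospital beds".

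**The concern.** AAW stay and total hospital stay exist for everyone randomised. Ward stay does not. It begins with a transfer that happens after randomisation and that the sensor is intended to prevent in some patients. Among patients who have a ward stay, the two arms need not be comparable. If the sensor works by sending home those who would have had brief ward stays, the patients left on the wards in the sensor arm are, on average, the longer-staying ones.

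Bed use is the trial's stated motivation. A published result that monitoring lengthened ward stay could therefore be an artefact of selection, reported from a trial in which monitoring saved ward days. The Abstract's outcome avoids this problem, but the section that defines the outcomes does not carry it over.

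**Working it through.** **1. The plan's own figures.** The article gives no LOS figure to reproduce. The only related numbers are safe direct discharge of 40% and 50% and the 768 patients derived from them. The unpooled normal approximation gives 385 per arm, 770 in total, and the pooled version gives 776. The stated sample size is therefore sound, but it does not bear on this point.

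**2. Inputs for the illustration, all assumed.**
- Transfer rates: p = 60% in controls and 50% with the sensor, so d = 10 percentage points avoided. These are the complements of the 40% and 50% in the Sample size section. Those figures concern *safe* direct discharge, so the complements also include patients discharged directly who later have a readmission, ED revisit or death. True transfer rates would be somewhat lower.
- Control mean ward stay among transferred patients: m = 4.0 days.
- Mean ward stay that the diverted patients would have had: a = 1.5 to 2.0 days.
- Stays of patients still transferred: unchanged by the sensor.

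**3. Comparison among transferred patients only.** The sensor-arm mean is (p·m − d·a)/(p − d).
- a = 1.5: (0.6 × 4.0 − 0.1 × 1.5)/0.5 = 2.25/0.5 = 4.5 days
- a = 2.0: (0.6 × 4.0 − 0.1 × 2.0)/0.5 = 2.20/0.5 = 4.4 days

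Against 4.0 days in controls, the sensor arm looks 0.4 to 0.5 days worse.

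**4. Ward days per randomised patient, zero if not transferred.**
- Controls: 0.6 × 4.0 = 2.40 days
- Sensor: 2.40 − 0.15 = 2.25 or 2.40 − 0.20 = 2.20 days

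The sensor arm is 0.15 to 0.20 days better.

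**5. When the sign reverses.** The transferred-only difference simplifies to d(m − a)/(p − d), and the per-randomised difference is −d·a. The two have opposite signs whenever a lies between zero and m. If avoided stays are as long as the average (a = m), the transferred-only mean does not move.

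**6. A wider range.** Now fix the stay of patients transferred in either arm at 4 to 6 days and let avoided stays run from 1 to 3 days. The control mean is (50 × retained + 10 × avoided)/60. With 5 and 1.5 days it is 265/60 = 4.42, against 5.00 with the sensor (+0.58). Per randomised patient the figures are 2.65 and 2.50 (−0.15). Over the whole range, transferred-only differences run from +0.17 to +0.83 days and per-randomised differences from −0.10 to −0.30 days.

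**7. Simulation of the 5 and 1.5 day case.** There were 3,000 runs with 400 per arm and log-normal stays (log-SD 0.7). Among transferred patients the sensor-arm mean was longer in about 95% of runs. It was significantly longer in about 34% by t-test, and in about 66% Mann-Whitney was significant with a longer sensor-arm median. No patient's stay had been lengthened.

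**8. The zero-coded reading.** With 40% of controls and 50% of sensor patients at zero, normality fails and the stated rule leads to Mann-Whitney. Of all between-arm pairs, 0.6 × 0.5 = 30% compare two actual ward stays. The other 70% are settled by transfer status alone (one zero, or a tie at zero). The test mostly re-examines direct discharge, and it returns no number of days. In the same simulation it favoured the sensor significantly in about 34% of runs, against about 8% for a t-test on mean days.

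**The case against.** The strongest reply is that the article never restricts ward LOS to transferred patients. It prescribes intention to treat for secondary outcomes, and even the per-protocol set keeps patients "regardless of their destination after AAW admission and the duration for which the wearable sensor was worn". Zero ward days for those discharged directly is compatible with that text. A reader might infer that the planned analysis is a transferred-only comparison with the wrong sign. That goes further than the documents: it is the natural reading of a ward-stay outcome, but it is not stated. This part of the objection stands, so the sign reversal must be presented as conditional.

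Next, the coding rule could sit in the full protocol or an analysis plan not shown. That is fair, and silence on zero coding alone would not be a finding. The mismatch between the Abstract and the Outcomes section is different, because both texts are in hand. It may be called mere labelling, since AAW and ward stay add up to hospital stay. But comparing two components separately is not comparing their sum, and only the sum is defined for every patient without a further rule.

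The illustration also rests on assumed stays and transfer rates, and the sensor may change who is transferred, and when, in other ways. The Introduction expects patients who need a ward to reach it sooner. This stands: the figures show what can happen, not what will.

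Finally, choosing between a t-test and Mann-Whitney by distribution is common for skewed stays, and the article promises no estimate of bed-days. Objecting to the rank test as such is largely preference.

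**Conclusion.** The point holds in a conditional form. The Abstract and the Outcomes section disagree on whether total hospital LOS is an outcome. The ward-stay outcome that appears instead is undefined for patients never transferred, and transfer is something the intervention is meant to change.

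A transferred-only comparison would not be protected by randomisation. Under the assumed inputs it shows 4.0 versus 4.4 to 4.5 days against the sensor, while ward days per randomised patient go from 2.40 to 2.20 to 2.25 in its favour. This requires that avoided stays be shorter than average and that other stays be unchanged. The first is plausible for patients whose need for a ward is equivocal, but the article does not quantify it. Zero coding restores the randomised comparison but, with the stated test rule, mostly repeats the direct-discharge result.

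It would go too far to say that the trial plans a biased comparison. This is a secondary outcome, worth correcting before analysis. The primary test and its sample size are untouched.

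**What to change.** Reconcile the Abstract and the Outcomes section by making total hospital LOS the LOS outcome: AAW plus ward stay, with ward stay zero if not transferred, in all randomised patients. Report the difference in mean days with a bootstrap or Welch 95% CI, without a normality pre-test. The planned rank test may be given alongside. Keep ward LOS among transferred patients as a description by arm, without a test. AAW LOS can stay as listed.

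The cost is a wording change in the protocol and analysis plan. The Data collection and management section already takes secondary outcomes from the electronic record, so no new data should be needed. Skewed stays will give a fairly wide interval for the mean difference, and the 8% figure above shows that it may well include zero. It would still estimate the bed use that motivates the trial, in groups that randomisation made comparable.

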### Statistics

For the descriptive analyses (e.g., characteristics of participants), continuous variables will be reported as mean with standard deviation for normally distributed data, and median with interquartile range for non-normally distributed data. For categorical variables, numbers and percentages will be reported.

For the primary outcome, the proportion of patients discharged home safely, directly after AAW stay, will be compared between the control and sensor group using a chi-squared test. Differences in LOS will be tested using Student’s *t*-test or Mann-Whitney test depending on the presence of a normal distribution. To assess whether the percentages of ICU admissions, RRT calls, and hospital admissions differ between the control and sensor groups, chi-squared or Fisher’s exact tests will be used, as appropriate. Intention-to-treat analyses will be used for the primary and secondary outcomes. Additionally, per-protocol analyses will be used to assess the effect of the sensor, adjusted for patients who receive a non-functional sensor due to technical reasons. All remaining patients will be included in these per-protocol analyses, regardless of their destination after AAW admission and the duration for which the wearable sensor was worn. An interim analysis for futility is planned once 50% of total amount of patients is included.

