### Sample size

Based on a preliminary internal investigation and insights of healthcare professionals working in the AAW, the proportion of the control group that is safely discharged was estimated to be 40%. As an increase to 50% was deemed to be feasible and clinically relevant, this proportion was used for the sensor group in calculating the sample size. The aim is to reject the null hypothesis stating that the proportion of patients that are discharged home safely directly after AAW stay is equal in the control and sensor groups. With a power of 80%, an *α* of 0.05, and equal group sizes, a total of 768 participants are required [19]. To achieve this number of patients with an assumed drop-out rate of 5%, the sample size is set to 800 patients, i.e., 400 in the control group and 400 in the sensor group.

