### Data collection and management

Data are collected from four different sources. Firstly, data on medical treatment, laboratory tests, patient characteristics, and primary and secondary outcomes, such as whether a patient was safely discharged, are retrieved from the Electronic Medical Record (EMR). Secondly, for the sensor group, wearable sensor data of the overall period up to 14 days are collected. Thirdly, supplementary data pertaining to the primary outcome, specifically healthcare usage after discharge (e.g., readmissions in other hospitals), will be obtained from patient questionnaires. The questionnaires also include information regarding the patient’s experience with the wearable sensor to assess feasibility. Since there is currently no validated questionnaire aligned with our study objectives, self-constructed questionnaires will be employed. Fourthly, data from questionnaires and interviews with healthcare professionals are collected at the end of the trial. Healthcare professionals will be selected using a stratified sampling method, ensuring a representative distribution of all specialties that operate in the AAW. These data will be used to investigate facilitators and barriers for implementing continuous monitoring in usual care in the AAW.

All collected data are protected according to data protection standards of the Netherlands and the European Union. All EMR and wearable sensor data are stored in pseudonymized form on secured hospital databases and are only accessible by authorized persons for this project. The questionnaire data are stored in pseudonymized form using the Research Manager platform (version 5.57.0). On signing the consent form, participants agree to the utilization of their data collected until the moment of potential withdrawal. Also, they agree to share relevant data with the involved researchers from the university or from regulatory authorities. Furthermore, patients are requested to provide consent for the utilization of their data in future studies pertaining to remote healthcare. No collection of biological specimens for storage will be conducted.

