### Substudy

As a substudy of this trial, algorithms to predict whether a patient can be discharged safely from the AAW or whether a patient will deteriorate in the AAW will be developed. These predictive algorithms will consider a range of hospital data, including demographics, vital signs, laboratory results, assessments (including EWS), medication use, care activities, and logistical information. Depending on the quality and characteristics of the data, which remain unknown until the trial is conducted, various artificial intelligence techniques, such as logistic regression and Random Forest, may be employed. Hospital data from both the sensor group and control group will be used to develop the algorithms. Furthermore, for the sensor group, additional algorithms will be developed that also utilize wearable sensor data to evaluate the additional value of the sensor. Additionally, for the sensor group, predictive algorithms for patient deterioration after hospital discharge will be developed, considering wearable sensor data and patient demographics. For these reasons, the wearable sensor will not be removed after AAW discharge, but will remain attached for the full extent of time specified by the manufacturer, which is 14 days. Predictive performances of the algorithms will be assessed by the area under the receiver operator characteristic curve, sensitivity, and specificity, among others.

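### The primary chi-squared test is valid but ignores baseline data the trial collects and treats as predictive of safe discharge; a prespecified adjusted risk difference would probably be more efficient

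*Protocol article*

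**What the plan says.** - **Primary analysis (Statistics).** The proportion discharged home safely, directly after the ward stay, "will be compared between the control and sensor group using a chi-squared test", by intention to treat. No covariate is named.
- **Primary outcome (Outcomes).** "The primary outcome is the difference between the control and sensor group in the percentage of patients who are safely discharged" directly after the ward stay. The outcome is therefore a between-group difference.
- **Population (Study setting, Intervention).** The article says that "the AAW accommodates a diverse patient population, including both surgical and non-surgical patients". The Intervention section also calls the population heterogeneous when explaining why physicians get no rule for reading the sensor data.
- **Allocation (Randomization).** 1:1, in blocks of four and eight in random order. No stratification factor is named.
- **Data available (Data collection and management, Substudy).** The medical record supplies "data on medical treatment, laboratory tests, patient characteristics, and primary and secondary outcomes". The substudy will build algorithms for safe discharge in both groups from hospital data that include "demographics, vital signs, laboratory results, assessments (including EWS), medication use".
- **Sample size.** 40% versus 50%, "With a power of 80"%, "an *α* of 0.05, and equal group sizes", giving 768 patients, raised to 800 for 5% drop-out. The null hypothesis is that the proportion "is equal in the control and sensor groups".

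**The concern.** The trial expects routine patient data to predict safe discharge well enough to build algorithms on them, yet its main comparison uses none of them. If age, specialty or early vital signs do predict the outcome, part of the variation between patients is explainable. An unadjusted comparison leaves that part in the error term. The cost is a wider interval and lower power than the same patients could give.

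The design has little to spare. After the assumed drop-out, 760 of 800 patients remain, fewer than the 768 the calculation asks for.

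Timing also matters. The Blinding section says that the data analysts are not blinded. If a case-mix imbalance appeared and covariates were chosen afterwards, that choice would be open to challenge. Covariates named in advance avoid the problem.

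**Working it through.** **1. Reproduce the stated sample size.** Inputs from Sample size: p0 = 0.40, p1 = 0.50, α = 0.05, power 80%, 1:1. Sidedness is not stated. Two-sided is inferred from the null of equality, and a one-sided test would need only 610.

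- Unpooled variance: n per arm = (1.960 + 0.842)² × (0.4×0.6 + 0.5×0.5) / 0.10² = 7.849 × 0.49 / 0.01 = 384.6, so 385 per arm, 770 in total.
- Pooled variance under the null: (1.960 × √0.495 + 0.842 × √0.490)² / 0.01 = 387.3, so 388 per arm, 776 in total.

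Both are within about 1% of 768. The sample size and the unadjusted test therefore agree.

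**2. Power of the planned test after drop-out.** 800 × 0.95 = 760, or 380 per arm.

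Power = Φ[(0.10 − 1.960 × √(0.495/n)) / √(0.490/n)]. With n = 380 this is Φ[(0.10 − 0.0707) / 0.0359] = Φ(0.815) = 79.2%. At n = 384 it is 79.7%.

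**3. Effect of adjustment.** If baseline covariates explain a share R² of outcome variance, the variance of the adjusted difference is about (1 − R²) times the unadjusted variance. This equals an unadjusted trial with 380/(1 − R²) per arm. The article does not give R², so the values below are assumptions. The unadjusted half-width is 1.96 × √(0.490/380) = 7.0 points, and each later value is multiplied by √(1 − R²).

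| Assumed R² | Power, 760 analysed | Equivalent unadjusted total, 760/(1 − R²) | 95% CI half-width (points) |
|---|---|---|---|
| 0 | 79.2% | 760 | 7.0 |
| 0.05 | 81.3% | 800 | 6.9 |
| 0.10 | 83.3% | 844 | 6.7 |
| 0.15 | 85.3% | 894 | 6.5 |

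**4. Check by simulation.** 768 patients, 4,000 trials per scenario, one normally distributed baseline covariate. Unadjusted test against a logistic model standardised to a risk difference with a robust standard error. Monte Carlo standard error is about 0.6 points for power near 80%, √(0.8 × 0.2/4000), and about 0.3 points for type I error, √(0.05 × 0.95/4000).

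| R² (AUC) | Power, unadjusted | Power, adjusted | Type I error, unadjusted | Type I error, adjusted |
|---|---|---|---|---|
| 0 (0.50) | 78.8% | 78.9% | 4.9% | 5.0% |
| 0.054 (0.63) | 80.4% | 82.3% | 4.9% | 4.8% |
| 0.144 (0.72) | 80.5% | 86.7% | 5.2% | 4.7% |
| 0.242 (0.79) | 79.6% | 89.3% | 5.4% | 5.4% |

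Both analyses hold the 5% level throughout. Adjustment gains power when the covariate predicts the outcome and loses none when it does not. The simulation uses one continuous covariate, so it does not test a model with a many-level specialty factor. That is one reason to group specialty.

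**5. Which covariates can be relied on.** Age is checked at screening (18 years or older). Table 1 sets ward admission rules by specialty, so specialty should be known at admission. An Early Warning Score before allocation is less certain. Usual checks are every 4 to 8 hours, patients have until 2 hours after ward admission to decide on participation, and allocation follows consent.

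**The case against.** The strongest reply is that nothing here is wrong. The chi-squared test suits a 1:1 trial with no named stratification factor, keeps its level, and is the analysis the trial was sized for. All of that stands. A reader might infer that heterogeneity, or chance imbalance in case mix, biases the test. It does not: the 5% level already allows for chance imbalance, and the simulation shows error rates near 5%.

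A second reply is that the gain is assumed. This also stands. The article gives no prognostic strength for any covariate. It enrols only patients whose destination the emergency physician cannot call, which could weaken baseline predictors. The substudy does not settle the matter: its algorithms are still to be developed, and some inputs, such as medication use, need not be baseline values. It is tempting to say that adjustment is sure to win back the power lost to drop-out. That holds only if the covariates have some predictive value.

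A third reply concerns reporting. A reader might infer that the plan will give no effect estimate because a chi-squared test yields only a p-value. The article defines the outcome as a difference in percentages, so that difference can be expected in the report. The interval method is detail that an article commonly leaves to the full protocol or analysis plan.

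Finally, recruitment began in December 2021, the analysts are unblinded, and a futility interim is planned at 50% inclusion. The article does not show whether the time for changing the primary analysis is still open. This limits when the fix can be adopted as primary. It does not remove the case for it.

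**Conclusion.** The point holds as a matter of efficiency. The article fixes an unadjusted primary test while collecting data it regards as predictive of the same outcome, in a population it describes as diverse. The test is neither biased nor inconsistent with the sample size.

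The loss runs from nothing, if the covariates are uninformative, to about 2, 4 or 6 points of power at R² of 0.05, 0.10 or 0.15 (81.3, 83.3 and 85.3 against 79.2). The half-width of the 95% interval shrinks by up to about half a point over that range. These figures rest on 40% versus 50%, 5% drop-out, a two-sided 5% test and the assumed R² values. The article does not support a claim that an Early Warning Score before allocation exists for every patient, so the conclusion does not depend on it.

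**What to change.** Before any comparative results are examined, including those of the futility interim, prespecify as the primary analysis:

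- a logistic model with arm, age and admitting specialty, with specialty grouped into a few categories fixed in advance;
- an Early Warning Score as a further covariate only if it is confirmed to be recorded before allocation;
- standardisation over the whole analysed sample to give the adjusted risk difference, with a robust 95% confidence interval and p-value.

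Keep the chi-squared test, with the unadjusted difference and its 95% interval, as a sensitivity analysis. If comparative results have already been seen, leave the chi-squared test as primary and report the adjusted analysis as supplementary.

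The cost is analysis wording and slightly more programming. No extra patients are needed, and age and specialty should need no new data collection. Because the analysts are unblinded, the covariates, their coding and the specialty groups must be written down and dated in advance.
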